## Abstract

**Background:**

Blepharospasm and hemifacial spasm are debilitating conditions that significantly impact on patient quality of life. Cyclical treatment with botulinum toxin injections offers temporary relief, but the duration of treatment efficacy is variable. The standard model of patient care defines routine fixed-time based scheduled treatment cycles which may lead to unnecessarily frequent treatment for some patients and experience of distressing symptoms in others, if symptoms return before the scheduled follow-up period.

**Methods/Design:**

A randomised controlled trial will compare a patient-initiated model of care, where patients determine botulinum toxin treatment timing, to the standard model of care in which care is scheduled by the clinical team. A sample of 266 patients with blepharospasm or hemifacial spasm will be recruited from Moorfields Eye Hospital (MEH), London. The trial will be accompanied by a mixed-methods evaluation of acceptability of the new service. Patients who meet eligibility criteria will be assessed at baseline and those in the intervention group will be provided with instructions on how to book their own treatment appointments. Patients in both groups will be followed up 3 and 9 months into the trial and all patients will be returned to usual care after 9 months to meet safety protocols. Primary outcome measures include disease severity (questionnaire), functional disability (questionnaire) and patient satisfaction with care (questionnaire). Secondary outcomes include disease-specific quality of life (questionnaire), mood (questionnaire), illness and treatment perceptions (questionnaire and semi-structured interviews), economic impact (questionnaire) and acceptability (questionnaire and semi-structured interviews).

**Discussion:**

This trial will assess the effectiveness and cost-effectiveness of a patient-led care model for botulinum toxin therapy. If the new model is shown to be effective in reducing distress and disability in these populations and is found to be acceptable to patients, whilst being cost-effective, this will have significant implications for service organisation across the NHS.

**Trial registration:**

UK Clinical Research Network (UKCRN) Portfolio 18660. Clinicaltrials.gov ID NCT102577224 (registered 29 October 2015)

## Background

Blepharospasm is a dystonia described by sustained, forced, involuntary closure of both eyelids, caused by muscle contraction. Hemifacial spasm occurs on one side of the face and can result in complete closure of one eye, and spasms across the cheek, face and neck. Hemifacial spasm, as its name implies, is unilateral, whereas blepharospasm always affects both eyes. Blepharospasm and hemifacial spasm are debilitating conditions, which carry the risk of functional blindness and can lead to appearance concerns, social embarrassment and isolation, depression and poor quality of life [1–3].

Botulinum toxin is the treatment used in standard care to alleviate spasms, but by their nature result in a cyclical pattern of relief and aggravation as the toxin wears off [4] and hence patients return for repeated injections. A recent systematic review indicated that the patient- reported benefits of botulinum toxin in blepharospasm ranged from no improvement to 96 % of patients reporting a significant relief in symptoms [5]. Evidence for the duration of benefit provided by repeated treatment is also markedly inconsistent [5]. Although the definition of benefit did differ between studies in this review, much of the inconsistency between studies remains unresolved. Despite this, a dosing interval of 3- to 4-monthly injections is typical for many different dystonias across the UK. However, the variation in response to this treatment may mean that some people are left experiencing debilitating symptoms until their next scheduled appointment and some are being seen more often than their symptoms would deem necessary. It would potentially be more useful, therefore, to explore alternative models of care based more closely on symptoms.

Patient-centred care is at the forefront of the NHS [6, 7] reflecting the shift away from the paternalistic model of healthcare. Patients are now encouraged to take a more active role in knowing and managing their health, and this is especially important in conditions such as dystonia where the reality of living with the condition is demanding. As a result patient-led healthcare services are becoming increasingly more common [8] and have the potential to address the inconsistencies found in the current botulinum toxin treatment regimen.

Studies of patient-initiated services, where the patient rather than healthcare professional initiates treatment and care, have shown promise. These services provide patients with information on when and how to access services, rather than having regular time-based scheduled appointments. A systematic review conducted by Whear et al. [8] synthesised the evidence for this model of care across three conditions: irritable bowel disease, breast cancer and rheumatoid arthritis. Overall, there were few differences in psychological or health-related quality of life outcomes between those initiating their own outpatient follow-up appointments compared to standard care, despite in many cases patients having less contact with healthcare professionals. Patient and clinician satisfaction were significantly greater in the patient-initiated services compared to regular appointment scheduling. Another more recent trial has also found significant reductions in healthcare utilisation without compromising clinical or psychosocial well-being [9].

Adopting a patient-led model of care has the potential to reduce morbidity and disability in patients with a short-term response to botulinum toxin. Conversely, this may also reduce unnecessary hospital visits and treatment for patients with a longer-term response. There is currently one patient-initiated, nurse-led botulinum toxin clinic running in the UK for patients with blepharospasm or hemifacial spasm [10], but is yet to be evaluated in comparison to usual care. Due to the variable nature of the duration of response to treatment, blepharospasm and hemifacial spasm are appropriate conditions in which to evaluate a service of this nature. This study, therefore, provides a unique opportunity to empower patients with dystonia to take control of their treatment scheduling and optimise the effects of botulinum toxin, by allowing them to seek treatment when they feel it is necessary rather than it being dictated by the clinical team.

The primary aims of this randomised controlled trial (RCT) are to: (1) investigate the effectiveness of a patient-led model for botulinum toxin treatment in maintaining a more stable pattern of disease severity and disability in patients with hemifacial spasm and blepharospasm in comparison to standard care, and (2) assess patient satisfaction with the new treatment model compared to standard care. The secondary aims are the assessment the impact of the service on psychosocial outcomes, including quality of life, illness perceptions, mood, acceptability and cost-effectiveness.

## Methods

### Study design

This study will be mixed methods adopting a concurrent embedded strategy [11], whereby a qualitative study will be embedded within a larger single-masked RCT, with the RCT as the dominant component. This design will provide information on effectiveness and also an in-depth assessment of the patient experience. The RCT will be a parallel-group, explanatory, superiority RCT designed to assess the effectiveness of a patient-initiated botulinum toxin service compared to usual care. Semi-structured interviews will be conducted with a sample of intervention participants in order to assess acceptability of the service.

### Randomisation

Randomisation (1:1) will be undertaken by a central randomisation service by the data management team at Moorfields Eye Hospital (MEH) in order to ensure the research fellow collecting and analysing the data is blinded to group allocation. Participants will be randomised to receive either treatment as usual or patient-initiated follow-up appointments. Randomly permutated blocks of varying sizes will be employed to ensure balance between treatment groups. Due to the nature of the nurse-led botulinum toxin clinic it will not be possible to blind the treating healthcare professionals from group allocation. The trial co-ordinator will staff the telephone line that participants in the intervention group will use to book their appointments and, as such, the trial co-ordinator will not be blinded to group allocation.

### Blinding

Due to the nature of the study, participants cannot be blinded to group allocation. The treating healthcare professionals will also not be masked. The research fellow responsible for entering data into the database and the statistician conducting data analysis will be blinded to participant allocation. All other members of the research team will be blinded to allocation throughout the study, prior to un-blinding at the end of analysis.

### Setting

The outpatient nurse-led botulinum toxin clinic at MEH.

### Inclusion criteria

Patients aged 18 years or over who have received a consultant-led diagnosis of hemifacial spasm or blepharospasm will be invited to take part in the trial. Eligible patients need to be on a stable dose of botulinum toxin treatment, defined as receiving toxin treatment over two previous cycles and free from side effects. Potential side effects of botulinum toxin treatment include ptosis, double or blurred vision, and foreign body sensations. Patients must possess the capacity to give informed consent to participate in the study, as judged by the specialist research nurse leading the clinic.

### Exclusion criteria

Patients will be excluded if they have significant co-morbidities (i.e. their predominant treatment is for another illness) and/or they are unable to communicate fluently in written and/or spoken English, to complete study measures.

### Intervention

Participants randomised to the intervention group will initiate their own treatment during the trial period (9 months). They will be given information about when and how to initiate an appointment in the nurse-led botulinum toxin clinic, in a leaflet sent to them by a trial co-ordinator after randomisation. Participants will be asked to contact the service when they feel their symptoms are returning at a sufficient level for them to seek medical help. Contact details for the service will also be provided along with information on how quickly an appointment will be made, with whom, and the procedure in the case of an emergency. Receipt of the leaflet will be followed by a telephone call from one of the research team to answer any questions participants may have. When participants in the intervention group contact the service to book an appointment they will be triaged by the trial co-ordinator. All patients with an activity score of 1 or above on the Jankovic Rating Scale (JRS; [12]) will be booked in to the next available slot within the twice-weekly nurse-led outpatient clinics, estimated within a 2-week period from the initial call. There will be no upper limit for the number of times participants in the intervention group can initiate an appointment. However, participants will be advised to wait 2 weeks after botulinum toxin treatment as this is the time it takes to reach effectiveness. It is, therefore, estimated that participants would not return to the clinic within 3 to 4 weeks of their previous appointment. All participants will be given an appointment at 9 months to meet safety criteria for any patients who do not seek an appointment during their participation in the trial.

#### Control group

Participants in the control group will receive usual care. This consists of scheduled appointments in the nurse-led outpatient botulinum toxin clinic, usually every 3 months.

### Outcomes

Participants will be in the trial for 9 months. An initial baseline assessment will be taken by a research fellow prior to randomisation; this will include the full range of measures. Self-report measures will be taken again at 3- and 9-month follow-ups.

At baseline, demographic information will be collected using self-report measures including: date of birth, gender, marital status, ethnicity, postcode, number of years of schooling, highest completed level of education and further education. Data will also be collected from the patients’ medical notes on diagnosis, year of diagnosis, duration of botulinum toxin treatment, number of previous cycles, frequency of previous cycles, last dose, and co-morbidities. The total number of botulinum toxin injections and dosage received by the patient across the trial period will be collected.

#### Primary outcome measures

##### Disease severity and symptoms

Disease severity and frequency of symptoms will be assessed using the JRS [12], a clinician-reported measure that consists of two subscales measuring symptom severity and frequency independently. A 2-point improvement in the JRS sum score is considered a clinically relevant improvement [13]. However, these criteria are only relevant for patients whose baseline scores are >2 on the JRS [13]. For patients with hemifacial spasm an additional rating scale for severity and frequency of cheek involvement will be included in the JRS, as suggested by Wabbels and Roggenkämper [14].

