#### Changes over time

In order to explore stability in the primary outcome measures over the treatment period, and change in satisfaction, quality of life, mood and illness and treatment beliefs, multilevel models (MLM) will be employed. Time will be nested within participants and to check the assumption that scores within a participant are highly correlated, the first MLM will include no predictors and a scaled identity covariance type for both level 1 and level 2 in order to calculate the intraclass correlation coefficient (ICC). Models will be fitted with a first order autoregressive (AR1) covariance structure. Restricted Estimate Maximum Likelihood (REML) methods will be used as these are preferred for smaller samples [35].

Trial arm (0 = control, 1 = intervention), time (0, 1, 2) and the interaction between trial arm and time will be entered as fixed effects in each model, with participant identification number as a random effect. A significant interaction term will be interpreted as evidence for differential treatment effectiveness. Pairwise comparisons will be performed in order to establish where the significant differences lie, using estimated marginal means and standard errors. Standardised adjusted effect sizes for group differences at each time point will be calculated using Hedges’ *g* along with 99 % confidence intervals (as *p* < 0.01) using the formula provided by Turner and Bernard [36]. Hedges’ *g* includes a correction factor for small samples which, if absent, may lead to a less accurate and upwardly biased effect size. These effect sizes are interpreted in the same way as Cohen’s *d* [37] (small = 0.20, medium = 0.50, large = 0.80).

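### If the cheek ratings taken only in hemifacial spasm enter the JRS sum, the pooled model analyses a primary outcome on two scales: the arm-by-time test stays valid, but weighting, time-point estimates and a little power suffer

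*Protocol article*

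**What the plan says.** The trial enrols two diagnoses together: "A sample of 266 patients with blepharospasm or hemifacial spasm will be recruited" (Protocol article, abstract, Methods/Design). The mix of the two is not stated.

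The first primary outcome is the JRS, described under Disease severity and symptoms as "a clinician-reported measure that consists of two subscales measuring symptom severity and frequency independently". The same paragraph adds: "For patients with hemifacial spasm an additional rating scale for severity and frequency of cheek involvement will be included in the JRS". It also gives one relevance criterion, "A 2-point improvement in the JRS sum score is considered a clinically relevant improvement", limited only in that "these criteria are only relevant for patients whose baseline scores are >2 on the JRS". Neither the range of the JRS nor a scoring rule for the extended version appears.

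Under Changes over time, the fixed effects are trial arm, then "time (0, 1, 2) and the interaction between trial arm and time will be entered as fixed effects in each model", with participant as a random effect. Diagnosis is not among them, although the Outcomes section lists it among the data taken from the medical notes at baseline. A significant interaction is the evidence of effectiveness. Hedges' g is reported for the group difference at each time point.

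On allocation, the Randomisation section says "Randomly permutated blocks of varying sizes will be employed to ensure balance between treatment groups". It mentions no stratification by diagnosis.

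**The concern.** Relevance is expressed on the JRS sum score, and the cheek ratings are to be included in the JRS. The natural reading is that a hemifacial patient's score sums more ratings, and so has a higher ceiling, than a blepharospasm patient's. Both are then analysed as one variable in one model.

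If so, a difference of one point is not the same quantity in the two diagnoses. The pooled difference weights the diagnoses by the length of their scale as well as by their numbers. The spread of scores at any time point contains a gap between diagnoses that has nothing to do with treatment, and this gap enters Hedges' g. A chance surplus of hemifacial patients in one arm moves that arm's mean at every time point. The economic analysis, which relates cost to change on the JRS, would inherit the same mixed unit.

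**Working it through.** **The plan's own figure first.** Table 2, Scenario 1: d = 0.25, ICC 0.3, 4 time points, 115 per arm, two-sided alpha 0.05, stated power 0.80.

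- SD of a participant mean over m time points, in SD units: sqrt((1 + (m − 1) × ICC)/m) = sqrt(1.9/4) = 0.689.
- SE of the arm difference: 0.689 × sqrt(2/115) = 0.0909.
- Power: Φ(0.25/0.0909 − 1.96) = Φ(0.79) = 0.785.

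This is within 2 points of the stated 0.80 and serves as the reference below.

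**Assumed inputs.** The article gives neither the JRS range nor the diagnosis mix. Let f be the hemifacial share (20 to 70%) and k the ratio of the hemifacial to the blepharospasm scale (1.5 to 2). The standardised effect is taken to be equal in both diagnoses.

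**Weighting.** The hemifacial share of the raw pooled effect is fk/(1 − f + fk). With f = 0.5 and k = 2 this is 1/1.5 = 67%, from half the patients.

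**Power.** With the level difference between diagnoses left out, because the interaction test removes it, the standardised effect is multiplied by (1 − f + fk)/sqrt(1 − f + fk²).

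| k | f | factor | Scenario 1 power |
|---|---|---|---|
| 1 | any | 1.000 | 0.785 |
| 1.5 | 0.2 | 0.984 | 0.772 |
| 1.5 | 0.5 | 0.981 | 0.770 |
| 1.5 | 0.7 | 0.986 | 0.774 |
| 2 | 0.2 | 0.949 | 0.742 |
| 2 | 0.3 | 0.943 | 0.737 |
| 2 | 0.5 | 0.949 | 0.742 |
| 2 | 0.7 | 0.966 | 0.757 |

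The loss is about 1 to 5 percentage points.

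**Does the missing diagnosis term harm the test?** Diagnosis is constant within a participant, so a level difference cancels in change over time. A simulation checked this: 150 runs, 115 per arm, the three time points of the model, f = 0.5, k = 2, ICC 0.3, random-intercept REML, complete data, no AR(1) term.

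- Arm-by-time estimate −0.529, SE 0.247, both with and without a diagnosis main effect.
- Standard error of the arm difference at the first time point: 0.241 without the term, 0.207 with it, about 14% smaller.
- Both diagnoses put on one scale: mean |z| of the interaction rises from 2.15 to 2.23.

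A main effect therefore helps the time-point comparisons but does not remove the mixing of units. A common score does.

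**Hedges' g at a time point.** Assume blepharospasm mean/SD of 3/1.5 or 4/2, both multiplied by k in hemifacial spasm, f of 0.3 or 0.5, and a true d of 0.25 in each diagnosis. For 3/1.5, k = 2, f = 0.5:

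- Raw difference: 0.25 × 1.5 × (0.5 + 0.5 × 2) = 0.5625.
- Variance within diagnosis: 0.5 × 2.25 + 0.5 × 9 = 5.625.
- Variance between diagnoses: 0.25 × (6 − 3)² = 2.25.
- g without adjustment: 0.5625/sqrt(7.875) = 0.200.
- g on the within-diagnosis SD: 0.5625/sqrt(5.625) = 0.237.

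Over all the combinations, g is 0.196 to 0.228 without adjustment and 0.236 to 0.245 with it.

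**Chance imbalance.** The SD of the shift in the arm difference is the gap in means × sqrt(2f(1 − f)/n), with n = 115. The smallest case is 1.5 × sqrt(0.42/115) = 0.09 points and the largest 4 × sqrt(0.5/115) = 0.26 points.

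**The 2-point criterion.** Taking ranges of 0–8 for the common ratings and 0–12 or 0–16 for an extended score (all assumed), 2 points is 25%, 16.7% or 12.5% of the range.

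**The case against.** The strongest reply is that the premise is not written down. The article never says the cheek rating is added to the sum. Included in the JRS could mean recorded beside the two standard subscales, and the scoring may be settled in the cited source or in the full protocol. This stands in part: summing is implied, not stated, so every figure above is conditional on it. It does not dispose of the point. The same article fixes scoring wherever comparability is at stake elsewhere: the BSDI is a mean over applicable items, CDQ-24 subscales are rescaled to 0–100, and the four symptoms added to the IPQ-R identity scale come with a new maximum of 18. Only the JRS, a primary outcome, gains ratings in part of the sample with no such rule, and the model terms are listed for each model.

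The second reply is that the missing diagnosis term does no harm to the planned decision. For the arm-by-time test this stands, as the simulation shows. It does not cover the time-point comparisons and Hedges' g, which the plan also reports.

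The third reply is that all the sizes rest on assumed shares, ratios, means and SDs. That is correct, and they are therefore given as ranges. Unstratified permuted blocks are also valid; the lack of stratification matters here only because it leaves diagnosis free to be unbalanced by chance.

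**Conclusion.** The point holds, conditional on the cheek ratings entering the sum. It is a moderate defect in the interpretability and efficiency of one primary outcome. Hemifacial patients get more weight than their number warrants, power drops by about 1 to 5 points, Hedges' g is diluted, and raw time-point differences can move by about 0.1 to 0.3 JRS points (one SD) through chance imbalance.

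A reader might infer more, and the documents do not support it:

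- **That the primary test is invalid, or loses precision in proportion to the added between-patient variance.** The random intercept takes up a constant level difference, so that variance is not a loss for the interaction.
- **That the 2-point criterion fails in one of the diagnoses.** The article limits it only by baseline score and does not name the population it came from. What can be said is that it is given for the sum score, with no value for an extended one. It enters neither the sample size, which rests on d of 0.25 to 0.4, nor the model, so only interpretation is affected.
- **That every outcome model needs a diagnosis term because of the cheek items.** Satisfaction, mood and the BSDI are not described as having items for hemifacial spasm only.

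**What to change.** State whether the cheek ratings enter the analysed JRS score. Define the primary JRS score as the severity and frequency ratings common to both diagnoses, report the cheek ratings separately for hemifacial spasm as a secondary result, and add diagnosis as a fixed effect in the JRS model. State that Hedges' g for the JRS is standardised by the SD within diagnosis; otherwise the covariate does not undo the dilution. Tie the 2-point criterion to the common score.

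The common score removes the mixing of units; the covariate sharpens the time-point comparisons and protects them from chance imbalance. If the cheek ratings were always meant to stay outside the sum, one sentence saying so replaces the scoring change.

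The cost is a scoring rule and one covariate; the ratings and the diagnosis are already collected. The downside is that the primary score no longer captures cheek involvement in hemifacial spasm, which is then seen only in the secondary report. The change should be fixed before allocation is unmasked.
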